| Intervention(s) | Intervention: Participants given personalised Lifestyle for Brain Health (LIBRA) score and profile based on their modifiable risk factors and access to In-MINDD on-line support environment. |
|  | Control: Generalised health information. Personalised Lifestyle for Brain Health (LIBRA) score and profile based on their modifiable risk factors and access to In-MINDD on-line support environment given to control group at end of study. |
| Key inclusion & exclusion criteria | Inclusion criteria:   - Registered with a participating practice - Age 40 – 60 on date of consent - Presence of any one (or more) of the following risk factors   - Depression – previous history OR active episode of minor depression as recorded on medical record – ***IF*** GP deems patient fit to participate   - Diabetes (diagnosis e.g. on a diabetes disease register)   - Hypertension (as per national guidelines)   - Obesity (BMI of 30.0 or above)   - Current smoker   - High cholesterol (as per national guidelines)   - Coronary heart disease (diagnosis e.g. on a CHD disease register)   - Self reported sedentary lifestyle   - Self reported lack of cognitive stimulation - Medically stable - Literate in language of the partner country where patient is recruited (English/Dutch/French as appropriate). - Access to the internet in order to communicate by email and access information online. |
|  | Exclusion criteria:   - Active episode of **major** depression, if GP deems patient too severely ill to participate, recorded in medical record or assessed using a validated assessment score e.g. HADS - People who are unable to give informed consent - People who have dementia |
| Study type | A multi-centre, primary care-based, investigator-blinded, randomised 6-month feasibility trial |
| Date of first enrolment | July 2014 |
| Target sample size | 150 per country; 600 in total |
| Recruitment status | Pending |
| Primary outcome | Global dementia risk score |
| Secondary outcomes | Change in individual risk factors |

1. ***Roles and responsibilities***

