At three months, participants will be asked to complete an on-line questionnaire about risk factor(s) they have selected and the steps and actions they have taken, if any, to reduce that or those risk factors. This questionnaire will address risk factors they selected, what they have learned about reducing that risk factor, what steps/actions they took to follow the advice given, how they have accessed those activities and how often and whether they are still participating in those activities. They will also be asked if they would be willing to be interviewed about their experience so far in In-MINDD. In addition, use of the In-MINDD support environment will be monitored remotely, e.g. how often they access the systems; for how long; and what sites they visit.

After six months participants will meet with the researcher or practice nurse again and update their information on the In-MINDD system in order to generate a final LIBRA score and profile.

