***Control arm of the trial.***

Participants in the control arm will receive a letter from the researcher telling them they are in the control arm; they will receive generic health information material e.g. on smoking cessation, increasing physical activity. Participants in the control arm will be asked to complete an on-line questionnaire at three months. (In order to maximise follow up rates participants who don’t complete the on-line questionnaire will be offered a telephone alternative.) They will be informed that we will contact them towards the end of the trial period, to identify anyone who may wish to be interviewed. At the end of the trial period they will meet again with the researcher and complete the profiler. They will receive a copy of their LIBRA score and profile and will be given access to the In-MINDD on-line support environment.

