***16c. Implementation of allocation***

The Robertson Centre will generate the allocation sequence. The research team in each partner country will enrol the patients into the trial. After the researcher has collected baseline data, they will assign patients to either the intervention or control arm of the trial by accessing the randomisation schedule either on-line or through use of a Smartphone app.

1. **Blinding**

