***17a. Trial blinding***

The trial is single-blinded; patients, practitioners and the researcher conducting qualitative research will know the arm to which patients are allocated, however the statisticians conducting the quantitative analysis will be blinded to study allocation.

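### The registration data call the trial investigator-blinded, but only the analysing statisticians are blinded and the six-month primary outcome is collected by people who know, or are placed to know, the arm.

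*Protocol*

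**What the plan says.** The Study type row of the registration data reads "A multi-centre, primary care-based, investigator-blinded, randomised 6-month feasibility trial".

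Section 17a, like Section 8, calls the trial single-blinded and explains the term. On one side, "patients, practitioners and the researcher conducting qualitative research will know the arm to which patients are allocated". On the other, "however the statisticians conducting the quantitative analysis will be blinded to study allocation". No other group is named as blinded.

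On allocation, Section 16c says: "After the researcher has collected baseline data, they will assign patients to either the intervention or control arm of the trial". Section 16b likewise has the research teams allocate, through an online tool. Under Section 11a the research team writes to each participant with the result. For controls the text is specific: "Participants in the control arm will receive a letter from the researcher telling them they are in the control arm".

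On the six-month visit, Section 11a says of the In-MINDD arm: "After six months participants will meet with the researcher or practice nurse again and update their information on the In-MINDD system". Of the control arm it says: "At the end of the trial period they will meet again with the researcher and complete the profiler". The profiler produces the global risk score, which is the primary outcome.

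**The concern.** A reader of the registration entry will take investigator-blinded to mean that whoever collects the outcome does not know the arm. That matters here because the outcome is exposed to reporting. Section 11a says that most of the profiler's background, health and habit data are self-completed. Mood, physical activity, cognitive activity and diet come from questionnaires. Participants know their arm. Those in the In-MINDD arm have been shown which risk factors need work, have been invited to set goals, and receive reminders before they answer the profiler again. Controls see no profile until the end.

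If the person running the visit also knows the arm, both participant reporting and assessor influence can differ between arms. Someone judging the trial by its label would wrongly think that the second route had been closed.

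**Working it through.** No arithmetic bears on this point. The check sets the relevant places side by side.

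1. **The label.** The registration data say investigator-blinded.

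2. **Who is declared blinded.** Sections 8 and 17a give patients, practitioners and the qualitative researcher as knowing the arm, and the statisticians as not knowing it. The researchers who recruit and follow up participants appear on neither list, so their status has to be read from the procedures.

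3. **Who allocates and announces.** Sections 16b and 16c have the country research team assign the arm once the baseline data are in. Section 11a has the research team send the allocation letter. The researcher role therefore knows the arm from the day of randomisation.

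4. **Who is present at six months.** The protocol gives three different accounts:
   - Section 11a text: researcher or practice nurse for the In-MINDD arm; researcher only for controls.
   - Summary schedule of assessments: researcher or practice nurse in both arms.
   - Participant timeline (CONSORT diagram): researcher in both arms.

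   None of these describes a separate or blinded assessor. The practice nurse is a practitioner, so is unblinded under Section 17a. Section 11a also allows a practice nurse to be the person who talks an In-MINDD participant through the LIBRA result. On the Section 11a text, someone who delivered part of the intervention could attend the outcome visit in one arm only.

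5. **How the outcome is obtained.** Section 18 says that participants complete the profiler questions and that this is repeated at the end of the trial. At baseline the researcher goes through data collection with the participant. For six months, the Section 11a text speaks of updating information in one arm and completing the profiler in the other. Nothing says that the self-report items are answered unaided.

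6. **Another sign of inconsistency.** Section 5d keeps representatives of the other partner countries off the steering committee because that committee is unblinded. This suggests that those teams were meant to be shielded from something, yet Section 16c has the team in each country assign the arms.

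Steps 2 to 4 leave no participant-facing investigator who is described as blinded. The label in step 1 is contradicted by the procedures, and steps 4 to 6 show that the procedures also disagree among themselves.

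**The case against.** The strongest reply is that this is a wording slip in one table. Sections 8 and 17a state openly, in a single sentence, who knows the arm and who does not. Participants cannot be blinded to an intervention of this kind, and Section 8 makes feasibility, assessed qualitatively, the principal aim. Much of the profiler is self-completed, so an unblinded researcher in the room matters less than one who rates the outcome. Section 5d may mean that partner teams were to be kept from pooled results, which is a form of blinding. All of this is fair. It limits how serious the point is, but it does not make the label true.

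Several stronger readings are tempting, and the protocol does not support them:

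- **The same individual allocates and assesses.** The protocol uses the same role and provides no separation, but never says that one person does both.
- **In-MINDD participants learn which answers lower their score.** Section 11a describes an overall score and a breakdown by risk factor. Item-level scoring is not described as shown.
- **The bias is a known fraction of the target effect.** The sample size section gives the target as 0.187 or 0.2. A reader might assume a bias of 0.05 to 0.10 SD and call it 25% to 50% of 0.2 (0.05/0.2 and 0.10/0.2). Nothing in the protocol supports that assumed range.
- **The plan has no way to see how far an effect rests on self-report.** Changes in individual risk factors are the secondary outcomes, and the statistical methods section applies similar models to them. Further detail is left to an analysis plan that is not shown.
- **A score built only from GP-record items would settle the matter.** The GP pro-forma is described only at baseline, diagnoses would hardly change in six months, and the practitioners supplying the data know the arm.

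**Conclusion.** The point holds as a misstatement of the design. The protocol claims investigator blinding and describes a trial in which only the statisticians are blinded and outcome collection is not. Reporting or assessor bias in the primary outcome cannot be excluded, and analyst blinding does not address it. Its size cannot be derived from the protocol, and none is claimed here.

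The conclusion assumes that the researcher who meets the participant at six months belongs to the team that assigned and announced the arm, or otherwise has access to the allocation. The text points that way and provides nothing to prevent it. If a separate blinded assessor was intended, the protocol does not say so.

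This should be corrected, but it does not undermine the randomisation. The registration data give recruitment as pending, so the change can be made before enrolment.

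**What to change.** - In the registration data, replace investigator-blinded with open-label with blinded statistical analysis. Use the same term in Sections 8 and 17a, keeping their list of who knows the arm and adding the country researchers to it.
- Reconcile Section 5d, Section 11a (both arm descriptions and the summary schedule), the participant timeline and Section 16c on who knows the arm and who attends the six-month visit. Name the same role for both arms.
- State that participants in both arms complete the self-report items at six months themselves, without researcher or nurse input.
- When interpreting the existing secondary analyses of individual risk factors, separate GP-supplied from self-reported components. This depends on the GP data being collected again at six months, which the protocol should confirm. It is supportive only, because those data are not blinded either.

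The cost is wording in a handful of places and an instruction to the field teams. No extra assessor is needed, and no new model is needed for risk factors already analysed. The downside is a less favourable design label.

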***5b. Name and contact information for the trial sponsor***

Trial sponsorship is only required in Scotland – the trial sponsor is:

[name]

NHS Greater Glasgow and Clyde

Clinical Trials Unit

1^st^ Floor

[name]

[name]

[name]

***5c. Role of study sponsor and funders, if any, in study design; collection, management, analysis, and interpretation of data; writing of the report; and the decision to submit the report for publication, including whether they will have ultimate authority over any of these activities***

The funder has no role in the design of this study and will not have any role during its execution, analyses, interpretation of the data, or decision to submit results. The funder and the sponsor are responsible for auditing study data.

***5d. Composition, roles, and responsibilities of the coordinating centre, steering committee, endpoint adjudication committee, data management team, and other individuals or groups overseeing the trial, if applicable***

In-MINDD trial co-ordination centre is the University of Glasgow. The lead is [name] [name]; the trial manager [name], in her role as the principal researcher for work package 3. Statistical and data management support is provided by [name], Robertson Centre for Biostatistics, University of Glasgow.

The trial steering committee will comprise COD, AMcC in Scotland. In addition, we will include [name] (Professor of Primary Care Research (General Practice and Primary Care), who is part of the IN-MINDD Advisory Group and [name] from Pintail. [name] will chair the trial steering committee.

The trial steering committee will meet three times: once as the trial is preparing to commence; once around the trial mid-point; and once when data are being analysed. These meetings will be conducted by video conference. The purpose of the trial steering committee will be to comment on the design and execution of the trial and to ensure that the processes set in place for execution, analysis and presentation of the findings are robust and transparent. The trial steering committee will also monitor the trial for adverse events (see section 22 – Harms). The trial steering committee will be unblinded to intervention allocation. For that reason, we will not include representatives from the other partner countries. However, a report on trial progress will be made to the IN-MINDD team after each meeting.

1. ***Background and rationale***

***6a. Background:*** Dementia is a serious loss of cognitive ability beyond what might be expected from normal ageing. Currently incurable, the onset and development of dementia can create an enormous sense of insecurity within individuals and their families. Research has demonstrated high levels of anxiety amongst middle aged and young-old individuals about their memory, compounded by the fact that the debilitation associated with dementia makes it one of the most feared conditions in relation to ageing ^1,2^. At a system level, the ageing demographics of many countries means that caring and treating dementia is a growing global burden; in Europe the total cost of dementia care in 2005 was estimated to be €130 billion^3^. In the UK, dementia costs the economy 23 billion Euros per annum, more than cancer and heart disease combined^4^. In Ireland, the economic and social costs of dementia have been estimated to be €1.6 bn per annum.

A number of risk factors have been identified which can enhance or reduce one’s risk of developing dementia^2,5^. While some of the principal risk factors are non-modifiable, such as age and genetic factors, a surprising number are modifiable. These include hypertension; cholesterol; obesity; alcohol consumption; smoking; and levels of physical and cognitive activity. Thus, a key message underpinning the In-MINDD study is that there are steps that individuals can take in mid-life to mitigate their potential risk of developing dementia in later life. This, however, means identifying effective ways of supporting individuals to make – and maintain – changes in health-related behaviours. This is known to be a challenging task. Utilising the power of the internet as a social support, In-MINDD seeks to test the provision of information on dementia risk coupled to access to an on-line support environment with patients in four European primary care systems.

The overall aims of In-MINDD are to: (i) develop a robust dementia risk model based on modifiable risk factors; (ii) implement this risk model in collaboration with patients and practitioners, by designing and supporting an on-line user environment; and (iii) test the feasibility and effectiveness of the In-MINDD system through a primary care-based feasibility randomised controlled trial.

Specific objectives are:

1. To formulate and validate a multi-factorial model of dementia risk using a combination of Delphi approaches and data mining of retrospective datasets;
2. To use this risk algorithm to produce a personalised risk reduction strategy, reflecting the patient’s risk profile, for endorsed by a GP or other primary care practitioner. This will be supported by an on-line environment giving the patient access to information and self-help materials.
3. To validate this approach on two levels: in terms of its usability and value to primary care clinicians’ and to assess patient adherence to the risk reduction strategy.
4. To publicise the modifiable nature of lifestyle risk factors for dementia.
5. To encourage dissemination to the public of the individual’s capability to modify his or her own risk of dementia through incorporation of this message into policy and health promotion campaigns.

In order to understand how the In-MINDD risk profiler and online support environment are used and the work required by both individuals and practitioners to embed this into everyday life and practice, the study will be underpinned by the use of Normalisation Process Theory ^6-8^. This is a sociological theory which helps us to understand how complex interventions become embedded and routinised into everyday practice (or not) and the work that individuals, both patients and health care professionals, have to do in order to sustain that activity.

***6b. Choice of comparators.***

Patients in the In-MINDD arm of the feasibility study will complete the on-line profiler which gather s information on their clinical history and on behavioural factors identified in WP1 as contributing, or alleviating, dementia risk e.g. mid-life obesity, smoking, cognitive activity. These data calculate a individual’s dementia risk score. Given the potential sensitivity and negativity associated with a dementia risk score, participants will receive this information in form of a personalised Lifestyle for Brain Health (LIBRA) score and profile (see Appendix)^[[1]](#footnote-1)^. This is a personalised profile highlighting those areas where they are doing well in terms of protecting their brain health and those areas where they can make sustainable lifestyle behavioural changes. Patients will have an opportunity to discuss their LIBRA score and profile and personalised plan with a GP or other member of the general practice team, such as a practice nurse – either face-to-face or by telephone. Following this consultation, they will also be given access to the In-MINDD on-line support environment. This will allow them to access information on health-related behaviours, for example advice on health eating; advice on physical exercise; links to smoking cessation services.

Where possible, there will also be some information on local services. So, for example, if someone decides that they wish to reduce their risk of developing dementia by increasing their physical activity or taking up an activity such a learning a language, they will be able to access information about available classes through the In-MINDD support environment. Since several lines of evidence indicate that setting goals is an important strategy for helping people to make lifestyle changes, the support environment also incorporates goal setting, which again is personalised for each individual according to their LIBRA profile. Participants will be able to set specific goals and will be able to self-monitor progress. They will supported by regular prompts and feedback regarding goal attainment. Goal attainment will be tracked by the system. Other on-line supports include an Ask the Experts feature and may include a closed forum on Facebook.

Patients randomised to the control arm will be given generic health information about health-related behaviour change e.g. in relation to smoking cessation, increasing physical activity. At the end of the 6-month feasibility trial period, they will be given their LIBRA profile and access to the In-MINDD environment. These patients will be free to discuss this information with their GP or practice nurse, if they wish.

1. ***Objectives***

The overall objectives for In-MINDD are noted in Section 6a.

The specific objectives for the feasibility RCT are:

1. To compare the effectiveness of the In-MINDD intervention compared with care as usual in reducing the overall risk of developing dementia and on individual risk factors.
2. To explore how patients use the In-MINDD intervention in terms of access to and time spent on the on-line environment.
3. To explore the feasibility of using the In-MINDD risk profiler and on-line support environment from the perspective of patients.
4. To explore patients understanding of, attitudes towards and experiences of obtaining their Lifestyle for Brain Health score and profile.
5. To explore the supports and barriers to embedding behaviour changes into everyday life, and whether or not the In-MINDD intervention helps or hinders patients make and maintain changes to individual health-related behaviours.
6. To explore the feasibility of using the In-MINDD risk profiler from the perspective of primary care practitioners.
7. To understand practitioner views of the utility of the Lifestyle for Brain Health score and profile and how they relate that information to patients.
8. ***Trial design***

In-MINDD is a feasibility randomised controlled trial. The trial is single-blinded; patients, practitioners and the researcher conducting qualitative research will know the arm to which patients are allocated, however the statisticians conducting the quantitative analysis will be blinded to study allocation. While it has been powered to detect a small effect size in relation to the primary outcome (i.e. reduction in overall dementia risk score, which will be indicated by changes in their LIBRA score/profile), the principal aim is to test the feasibility and workability of the approach in routine primary care. This will be assessed through the use of qualitative methods, underpinned by the theoretical approach of Normalisation Process Theory.

1. ***Study setting***

The In-MINDD feasibility RCT will be based in four different primary care systems in Europe, namely: Ireland; The Netherlands; France; and Scotland. The lead organisations in each country are:

Ireland – Dublin City University (DCU)

The Netherlands - Maastricht University (MU)

France - Université Nice Sophia Antipolis (UNS)

Scotland – University of Glasgow (GU)

Within each country, the work will be located in general practice/family practices. A total of 6 - 10 general practices will be recruited in each country; within each practice, up to 25 patients will be recruited, giving 150 research participants per country and a total study population of 600 patients across the four countries. General practices will be selected on their interest in taking part in the study.

1. ***Eligibility criteria***

